**Discussion:**

Our preliminary data indicates that most outcome variables before and after the intervention are not stationary, and accordingly we model this behaviour using linear mixed-effects (lme) models which can flexibly model within-group correlation often present in longitudinal data with repeated measures. We expect reduced incidence of unscheduled hospitalisation as well as improvement in the management of chronically ill patients, leading to better and more cost effective care. Advanced data analytics together with clinical decision support will allow telehealth to be deployed in very large numbers nationally without placing an excessive workload on the monitoring facility or the patient's own clinicians.

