### Classical BACI designs and extensions

Because of the temporal nature of health data and the underlying trends caused by the increasing burden of chronic disease with increasing age, before and after comparisons can be difficult or inconclusive. In this study we will have available patient data for a period of 4.5 years including the period of the intervention which may vary from 6–18 months.

Since standard BACI design cannot be used when study variables trend over time, we adopt a mathematical approach using a mixed linear effects model (*lme*) to assess the intervention while trying to adjust for the time varying mean in simple ways. The *nlme* library in the statistical package R is used to perform the analysis according to the methods of Pinheiro et al. [39].

The Test patients will be matched with one or two controls and the relative movement of Test patients’ outcomes before and after the start of the intervention will be compared to that of their Control patients. The before-and-after comparisons use control patients to adjust for background variations in such variables as public health policy impacting on costs and even for example, climatic conditions during the before and after intervention period.

Let *y*_*ijk*_ be any of the variables to be analysed, such as for example, the PBS/MBS/Hospital costs value per unit time period (month) at time k during period *i* (before or after the intervention), for patient *j* (control or intervention patient). The model for the response value is given by

where:

 *μ* is the overall mean *α*_*i*_ is the effect of period (before and after) τ_k(i)_ is the repeated measures within periods (assumed to be a random effect) β_j_ is the effect on jth matched patients (intervention or control) (αβ)_ij_ is the interaction between period and matched patient groups θ is the overall slope relating to time in months if no differentiation is made between the groups (B-A, C-I) θ_ij_ is the slope relating to time (k) in months for the various combinations of the groups (B-A, C-I). e_ijk_ is the random error term of the model that is assumed to be normally distributed with homogeneous variance.

Assumptions made:

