 Log of cost plus one will be treated as normally distributed with log of the number of days in the month as the offset. Sometimes the square root transformation may be used to stabilise the variance. We are hoping there are not too many zero cost periods or zero counts. If this fails we will use the zero adjusted inverse Gaussian distribution for the model – fitting them using the **gamlss** (package in R) using random() for including random effects [40]. τ_k(i)_ is a random effect in the above model that is assumed to be normally distributed with mean zero and constant variance. The assumption in the previous dot point and the assumption for e_ijk_ in the model thus assumes that measurements made at the same time segments (e.g., on the same quarter) have the same correlation and homogeneous variances for all repeated measures. The above model treats the study as a fully-designed experiment with the appropriate randomisation. However, this is seldom the case because most impact studies are observational in nature. The assumption is that each measurement for the intervention patients is matched with a measurement for one or more control patients. This blocking is expected to control for the non-randomisation in the design. The complexity of this analysis can be greatly reduced by taking the differences between the Test and Control measurements The model above tests whether a significant change has occurred by testing the significance of the interaction term of the model for the before after indicator variables and the control-intervention indictor variable. For example if the coefficient for intervention patients and after intervention duration has lower insured costs that before the intervention after adjusting for controls, then the intervention has had a significant impact on costs. The random effects terms and random error term are assumed to be uncorrelated in time. The control patient is generally selected to control for all covariates. In this study this means that control patients should be identical to the intervention patient in terms of age, gender, SEIFA index and major comorbidities. The samples are selected over time (therefore they are time series rather than repeated measures made at the same time). So it may seem unlikely that the model errors will be independently distributed but hospital costs are measured a month apart and this should be enough to for the assumption of independence to be valid. The assumption that all repeated measures have the same variance is unlikely to be true. If the gamlss package is used then this change in variance can be accounted for. Although theoretically longitudinal data structures can be modelled by random effects in gamlss [40] but at present no computationally feasible implementation for large sample sizes and complex models exists. Assume that the trend in the response variable over time is approximately linear. This assumption is likely to be reasonable over the 5 year study period, but is unlikely to be true for longer time periods.

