**Table 6 Tab6:** **Power calculations for some selected variables**

Outcome measure all on the monthly scale	Effective sample size?	Assumed normal distribution	Shift amount (K)	SPower
PBS Total cost	30	Log(PBS Total cost+1)	1	1.00
MBS out of hospital costs	30	Log(MBS out of hospital costs+1)	1	1.00
MBS in hospital costs	30	Log(MBS in hospital costs+1)	1	0.84
Number of hospital admissions	30	Square root the number of hospital admissions	0.5	0.99
Number of GP visits during working hours	30	Square root of number of GP visits during working hours	0.5	0.89
Number of GP visits outside of working hours	30	Square root of number of GP visits outside of working hours	0.1	0.50
Total number of GP visits	30	Square root of total number of GP visits	1	0.97
Total number of either Specialist, Psychiatric, Allied Health visits and Procedures	30	Square root of total number of either Specialist, Psychiatric, Allied Health visits and Procedures	1	0.77
Total number of Laboratory tests	30	Square root of total number of Laboratory tests	1	0.97
Number of Laboratory	30	Square root of number of Laboratory	1	0.96
Tests		Tests		

The actual results may be much more complicated than this because the differences between the outcome variables may be auto correlated. This is particularly true if the test patient and the matched control patient outcome measures have different time series trends. Testing of whether the matched differences are auto correlated will be carried out when data becomes available but is not expected to be a significant problem.

The actual results may be much more complicated than this because the differences between the outcome variables may be auto correlated. This is particularly true if the test patient and the matched control patient outcome measures have different time series trends. Testing of whether the matched differences are auto correlated will be carried out when data becomes available but is not expected to be a significant problem.

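### The BACI mixed model, as its terms are listed, carries no correlation between months of the same patient, and monthly spacing does not justify leaving it out

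*Protocol article*

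**What the plan says.** All of the following is in the protocol article; the model is in the section Classical BACI designs and extensions. The equation itself is not in the text at hand, but its legend and the assumptions are.

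- The only term declared random, apart from the error, is τ_k(i), which "is the repeated measures within periods (assumed to be a random effect").
- Its meaning is given in the assumptions: "measurements made at the same time segments (e.g., on the same quarter) have the same correlation and homogeneous variances for all repeated measures". The shared element is the time segment, not the patient.
- β_j "is the effect on jth matched patients (intervention or control"), and the intervention is judged by "testing the significance of the interaction term of the model for the before after indicator variables and the control-intervention indictor variable". On that wording j is a two-level group.
- Slopes θ_ij are included for each period-by-group combination.
- "The random effects terms and random error term are assumed to be uncorrelated in time". The article grants that independent errors may look unlikely, then accepts them because "hospital costs are measured a month apart and this should be enough to for the assumption of independence to be valid".

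Three other places bear on this. The abstract's Discussion favours mixed models because they "can flexibly model within-group correlation often present in longitudinal data with repeated measures". Power calculations admits that "differences between the outcome variables may be auto correlated" and promises a test for it, but expects no significant problem and names no remedy. Data analysis says valid comparisons are on matched Test-Control pairs, with multiple controls averaged, and uses a one-tailed paired t-test for intervention effects.

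**The concern.** Patients in this cohort will differ persistently in severity, in rate of decline and in how their use of services changes. The eligibility table admits six diagnostic groups and two different admission-rate thresholds, and the five sites use different models of care. Months from one patient therefore resemble each other however far apart they lie. Serial correlation adds to this, because an exacerbation in one month raises costs in the next. The spacing argument also speaks only of hospital costs, whereas the model is meant for any outcome variable, including PBS and MBS costs.

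The article takes standard errors, p-values and an estimate of savings from this model, having adopted it because standard BACI cannot handle trends. If within-patient correlation is left out, the data are credited with the wrong amount of information. Either the false-positive rate exceeds its nominal level or power is lost, and the plan gives no way to tell which.

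**Working it through.** **The plan's own figures.** Table 6 gives power for a matched-pair t-test with an effective sample size of 30 and no autocorrelation (for example 0.99 for admissions, shift 0.5 on the square-root scale). σ and ρ appear only as symbols, so the table cannot be reproduced. Nothing below depends on it.

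**Inputs from the article.** 125 Test and 250 Control patients; 4.5 years of data, so 54 months; an intervention period of 6 to 18 months (12 used here, hence 42 + 12); level 0.05, one-sided. The article states that level for the paired t-test; applying it to the mixed-model term is an assumption.

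**Assumed inputs, not in the article.** ICC 0.3 (intercept SD 0.65 with residual SD 1: 0.65² / (1 + 0.65²) = 0.30); AR(1) coefficient φ from 0 to 0.7; patient slope SD 0 or 0.2 a year; a common start, so that the shared month effects cancel between groups.

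**Method.** Let Z hold the intercept, the after-indicator, time, and time × after. Let V be the covariance of one patient's 54 months:

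V = σ_b² J + σ_e² R(φ) + σ_s² tt′

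- True variance: (Z′Z)⁻¹ Z′VZ (Z′Z)⁻¹
- Variance the listed model reports: s² (Z′Z)⁻¹, with s² = trace(V)/54
- r = true SE / model SE; false-positive rate = 1 − Φ(1.645 / r)

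The number of patients cancels from r.

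**A case checkable by hand.** With patient intercepts alone, r = √(1 − ICC) = √0.7 = 0.837. Then 1.645 / 0.837 = 1.97, and the rate is 0.025.

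**Results for the period-by-group step, θ_ij slopes fitted, 42 + 12 months, ICC 0.3 except in the first row:**

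| Within-patient structure | r | One-sided rate |
|---|---|---|
| None (ICC 0) | 1.00 | 0.050 |
| Intercepts only | 0.84 | 0.025 |
| Intercepts + slopes, SD 0.2 a year | 0.82 | 0.022 |
| AR(1) 0.3 | 1.05 | 0.059 |
| AR(1) 0.5 | 1.22 | 0.089 |
| AR(1) 0.5 + slopes | 1.19 | 0.084 |
| AR(1) 0.7 | 1.39 | 0.118 |

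The slope-change term behaves alike: 0.025, 0.059, 0.089 and 0.116 for intercepts only and φ = 0.3, 0.5, 0.7.

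**Sensitivity.**
- ICC alone at 0.1 / 0.3 / 0.5: step rate 0.041 / 0.025 / 0.010.
- Intervention period, φ = 0.5: 0.062 with 6 months, 0.098 with 18. With φ = 0.7: 0.072 and 0.137.
- Without the θ_ij terms, 12 months: about 0.07 for φ = 0.3, 0.113 for φ = 0.5, and 0.11 (simulated) for random slopes.
- Staggered starts, simulated without slope terms (400 runs, Monte Carlo error about 0.011): 0.06–0.07 with ICC 0.3–0.5 alone, 0.09 with φ = 0.3, 0.16 with φ = 0.5. One before-after change per matched set held 0.035–0.063 in every scenario. Adding only a patient intercept left 0.11–0.24 under autocorrelation or patient-specific change.

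**The case against.** The strongest reply is that the model cannot be fully known. The equation is absent from the text at hand, and the response is defined for patient j, so β_j might be a patient effect. The references to a control-intervention indicator make the group reading more likely. Even on the other reading, a patient intercept leaves serial correlation and patient-specific change unmodelled, and the simulation shows that this is not enough.

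A second reply is that the model may be meant for one mean value per group per month, or for Test-Control differences, which the article mentions as a simplification. With group means, patient intercepts would do no harm to the standard error, but serial correlation still would. Differencing removes a set-level effect but leaves many months per set treated as independent.

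Third, an autocorrelation check is planned. That softens the point, but a check without a consequence changes no analysis.

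Some stronger readings are tempting and are not supported:

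- *That 375 × 54 = 20,250 patient-months are declared independent.* The article nowhere gives the analysis unit in those terms.
- *That matching is ignored.* Data analysis makes the matched-pair test the test of the intervention, and the model section invokes blocking and differencing. The gap lies in the listed mixed-model terms. The paired test avoids the problem, but only if each set contributes one value, which is not stated.
- *That differing patient trends always make the standard error too small.* With the θ_ij slopes the article includes and a common start, random linear slopes leave the step test conservative (0.022). The inflated rate of about 0.11 belongs to a contrast without those slopes.

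**Conclusion.** The concern holds in this form: the listed model has no term for correlation between months of the same patient or matched set, and the reason given for independence is not valid. If it is fitted to patient-level monthly data, its standard errors and p-values for the BACI terms will be wrong whenever such correlation exists, apart from chance offsetting of opposing errors.

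The direction is not fixed. Under the assumed values, with the slopes fitted and 12 months of intervention, the one-sided 0.05 step test runs from about 0.02 (lost power) to about 0.12 (more than double the nominal rate). Dropping the slope terms raises the rate where there is serial correlation or trend heterogeneity.

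This rests on the legend and assumptions rather than the equation, and on ICC, AR(1) and slope values that the article does not supply. A reader should not conclude that false positives are necessarily inflated. The supportable conclusion is that the reported precision cannot be relied on in either direction. The repair is cheap and should be made before analysis.

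**What to change.** In nlme, which the article already names:

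1. Add random intercepts for matched set and for patient within set.
2. Add patient-level random effects for period and for the time slope. An intercept alone is not enough.
3. Use corAR1 residuals within patient.
4. As a check, report either cluster-robust standard errors by matched set or a paired analysis with one before-after change per set. State that each set contributes one value to any paired t-test.
5. Say what follows from the autocorrelation check, and delete the statement that monthly spacing makes the errors independent.

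The cost is a few extra terms in software already chosen, longer fitting, possibly wider intervals and some risk of non-convergence. If the full model does not converge, fall back to the one-change-per-set analysis, named in advance. That analysis held its level in the simulations; the extended nlme model was not itself simulated.

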
These models will be fitted using the nlme package in R [39].

A hypothetical scenario is modelled schematically in Figure 5 below according to principles and assumptions outlined above.

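### The lme model keeps an equal-variance assumption that the plan calls unlikely to be true, states no variance structure in nlme, and contradicts itself on whether gamlss can help

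*Protocol article*

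**What the plan says.** All of this is in the protocol article under Classical BACI designs and extensions.

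- The error term "is the random error term of the model that is assumed to be normally distributed with homogeneous variance". The list of assumptions extends this: measurements in the same time segment are taken to "have the same correlation and homogeneous variances for all repeated measures".
- Later in that list the plan doubts this: "The assumption that all repeated measures have the same variance is unlikely to be true".
- The remedy attached to the doubt is conditional: "If the gamlss package is used then this change in variance can be accounted for". The next sentence says of longitudinal random effects in gamlss that "at present no computationally feasible implementation for large sample sizes and complex models exists".
- The first item of the list plans gamlss for another purpose. If there are too many zero months, a zero-adjusted inverse Gaussian model will be fitted in gamlss, "using random() for including random effects".
- That item also offers a transformation: "Sometimes the square root transformation may be used to stabilise the variance".
- After the list: "These models will be fitted using the nlme package in R". No variance function is mentioned.

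The same section gives 4.5 years of data per patient, of which 6 to 18 months are intervention. It says the effect is judged by the interaction of before/after with control/intervention, and that standard errors, t-values and p-values will be reported for all model parameters.

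**The concern.** The standard error of the interaction is built from one residual variance pooled over groups, periods and months. The plan doubts that this single variance exists, but the model it commits to has nothing to accommodate the doubt.

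Unequal variance does most harm when the compared stretches differ in length, as they do here. The pooled estimate is dominated by the long before period, while the uncertainty of the contrast comes mainly from the short after period. If the after months are noisier, the standard error is too small and the test too liberal. If they are quieter, it is too large and power is lost.

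A change in variance is plausible in this design. Patients are selected on recent unplanned admissions (Table 1), a trend with age is expected, and the share of zero months affects the spread of log(cost + 1). None of this fixes the direction.

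**Working it through.** The plan gives no variance ratio, so there is no figure of its own to reproduce. The Table 6 powers do not help, because the standard deviations and correlations behind them are not shown. What follows shows the possible size only.

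**Inputs from the article**
- Total span: 4.5 years = 54 months.
- After months n_a = 6, 12 or 18, so before months n_b = 48, 42 or 36.
- Nominal level: one-sided 5%, critical value 1.645. The Data analysis section states this for the matched pair t-test; using it for the lme test is an assumption.

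**Assumed input**
- r = after variance divided by before variance of the monthly Test minus Control difference, taken on both sides of 1.

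**Formulas** (before variance set to 1, months independent as the plan assumes; the number of pairs scales both standard errors alike and cancels)
- Pooled variance: p = [(n_b − 1) + (n_a − 1)r] / (n_b + n_a − 2)
- Model standard error: √[p(1/n_b + 1/n_a)]
- True standard error: √(1/n_b + r/n_a)
- True level: 1 − Φ(1.645 × model SE / true SE)

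**Worked case, n_a = 12, r = 2**
- p = (41 + 22)/52 = 1.212
- Model SE = √(1.212 × 0.1071) = 0.360
- True SE = √(0.0238 + 0.1667) = 0.436
- Ratio = 0.826; true level = 1 − Φ(1.358) = 8.7%

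**Mean-shift results**

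| After months | r | Model SE / true SE | True one-sided level |
|---|---|---|---|
| 6 | 2 | 0.762 | 10.5% |
| 12 | 2 | 0.826 | 8.7% |
| 18 | 2 | 0.892 | 7.1% |
| 6 | 0.5 | 1.309 | 1.6% |
| 12 | 0.5 | 1.210 | 2.3% |
| 18 | 0.5 | 1.120 | 3.3% |

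At r = 1 the level is 5% throughout.

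The planned model also has slopes by group and period, and Figure 5 is described as showing a slope change. The same comparison for a before/after slope change, using least squares with an intercept and slope in each period, gives 11.3%, 10.0% and 8.5% at r = 2 for 6, 12 and 18 months. At r = 0.5 it gives 1.1%, 1.5% and 2.2%.

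**The gamlss statements side by side.** One item relies on gamlss with random effects if zeros are too many. Another says longitudinal random effects in gamlss have no feasible implementation for large samples and complex models. The planned data are at most 375 × 54 = 20,250 patient-months, and the article does not say whether that counts as large. If it does, the zero fallback is in doubt as well. If it does not, nothing explains why the variance problem is left to an nlme fit with equal variances.

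**The case against.** **Other measures are named.** A reader might infer that gamlss is the only protection the plan offers. It is not: a square root transformation to stabilise the variance is named, costs are logged, and Table 6 lists a log or square root scale for every outcome. That stands. But the square root is optional in the text and not linked to the admission. It handles variance that rises with the mean, not a general change between periods or groups.

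**gamlss is not flatly ruled out.** A reader might also infer that the plan declares its own remedy infeasible. The sentence is limited to large samples and complex models, and the plan keeps gamlss for excess zeros. The supportable criticism is that the two statements do not fit together.

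**No direction is known.** The article gives no variance ratio and does not say which period is noisier. It cannot be said that the type I error is inflated; the test may equally be conservative.

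**The paired t-test is a different matter.** The Data analysis section relies on matched-pair t-tests. If each pair contributes one before-after change, the test estimates the variance of that change directly and is not distorted in this way. That stands and confines the point to the lme interaction test.

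**Detail may sit elsewhere.** The exact form of a variance function could be left to an analysis plan not shown. But this article fixes the error structure, names the package and doubts the assumption, so the point concerns what is stated.

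**Conclusion.** The point holds for the lme before/after by control/intervention test. The plan bases its standard errors on an equal-variance assumption that it considers unlikely, ties to it a remedy whose feasibility it questions, and moves to nlme without a variance structure.

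In the mean-shift illustration, a twofold variance difference between periods moves a nominal one-sided 5% test to between 7.1% and 10.5% if the after period is noisier, and to between 1.6% and 3.3% if it is quieter. These figures rest on assumed ratios, independent months, one common intervention length per row and a contrast simpler than the planned model. They show that the assumption matters with periods this unequal; they do not estimate the trial's actual error rate. The documents do not support a claim of inflated false positives, nor a claim against a t-test on one change per pair.

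**What to change.** 1. In the planned nlme model, specify a residual variance function by group and period (for example varIdent), so that Test and Control, before and after, each have their own residual variance.
2. As a check, report standard errors clustered on the matched set for the interaction.
3. Reconcile the gamlss statements: say whether gamlss with random effects is usable at this trial's size. If it is, keep it as the fallback for excess zeros; if not, name another.
4. Say for which outcomes the square root transformation will be used, and do not present it as the answer to variance that changes between periods.

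The variance function is one argument in a model call already planned. The clustered standard errors are a small separate estimation step. Neither needs more patients, data or follow-up, and the text change is a few sentences.
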